Once the collective intelligence output becomes available for a case, the study team randomizes it to the intervention or control cases. The study team assigned each case a unique study identification number for tracking purposes. Using a random number generator in blocks of four, we will randomize half of the cases, for each clinician, to an intervention group in which the clinician will receive a collective intelligence output between 60 and 80 hours from the time the clinician saw the patient in the clinic (ie, within 24-36 hours of case entry). For cases randomized to the controlled group, Human Dx will generate collective intelligence, but it will not be shared with the clinician. Clinicians will complete an online postvisit questionnaire for all of their cases (control and intervention) that provides their initial impressions of the case (eg, differential diagnosis and perceived case difficulty) and level of diagnostic confidence. The questionnaire for cases assigned to the intervention group includes additional questions that the clinician will answer after reviewing the collective intelligence output to assess the effect of the output on their diagnosis, plan, and confidence. The study scribes and the *contributors* on Human Dx will be blinded to case randomization.

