#### Exploratory Clinical Outcomes

We will measure and analyze specified, additional outcomes that are relevant to the diagnostic process. We will define diagnostic accuracy as having the correct diagnosis listed in the top 3 answers of the collective intelligence output (for intervention cases) or in the top 3 of the clinician’s list of possible diagnoses collected via survey data (for control cases). In addition, we will measure the number of diagnostic tests related to the initial complaint, ordered by the clinician within 30 and 90 days of the case presentation, and the number of unexpected visits (drop-in, urgent care, or emergency room) related to the initial presentation within 14 and 30 days of the index visit. Unexpected visits have been associated with higher risk of diagnostic error [1]. We refer to these as exploratory outcomes because we expect them to be highly variable both within and between clinicians and do not know whether we will have the statistical power to analyze them. Descriptive analyses of these outcomes may generate hypotheses for future study.

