#### Exploratory Analyses

We will perform mixed-effect multivariable logistic regressions to compare diagnostic confidence, T2Dx, and diagnostic accuracy of intervention versus control cases, accounting for clustering by clinician and adjusted for baseline diagnostic uncertainty, perceived case difficulty, patient age, race, gender, number of comorbid conditions, type of visit (new, returning, drop-in, or urgent care), and primary care clinician characteristics such as professional degree (NP vs MD), specialty (family vs internal medicine), and years of experience. We have chosen covariates a-priori based on clinical judgment. For cases randomized to the intervention, mixed-effect bivariate logistic regressions will compare physicians’ diagnostic accuracy before and after reviewing the collective intelligence, adjusted for the aforementioned clinician characteristics. We will use bivariate and multivariable linear regressions to compare the number of diagnostic testing and use logistic regressions to compare the occurrence of unexpected clinical visits at 30 days between intervention versus control cases.

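### The models for test counts and unexpected visits omit the clinician, within whom cases are randomised, so their tests are conservative to the extent that these outcomes cluster by clinician

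*Protocol article*

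**What the plan says.** Under Selection, Entry, and Randomization of Clinical Cases, the protocol article makes the clinician the randomisation stratum: "Using a random number generator in blocks of four, we will randomize half of the cases, for each clinician, to an intervention group".

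Under Exploratory Analyses, one group of outcomes is analysed with that structure in the model: "We will perform mixed-effect multivariable logistic regressions to compare diagnostic confidence, T2Dx, and diagnostic accuracy of intervention versus control cases, accounting for clustering by clinician". The before-and-after accuracy comparison in intervention cases is also mixed-effect. The closing sentence of the section treats the remaining two outcomes differently: "We will use bivariate and multivariable linear regressions to compare the number of diagnostic testing and use logistic regressions to compare the occurrence of unexpected" visits at 30 days. Neither clause mentions a random effect, clustering or any clinician term.

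On the exploratory outcomes, which include these two, the Exploratory Clinical Outcomes section says: "we expect them to be highly variable both within and between clinicians and do not know whether we will have the statistical power" to analyse them. The Multiple Hypothesis Testing section promises 95% CIs for every point estimate and treats these analyses as hypothesis generating.

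**The concern.** Each clinician contributes about equal numbers of intervention and control cases. A clinician who orders many tests does so in both arms, and that habit drops out of the arm difference. A regression without the clinician still counts the variation between clinicians as noise. Its standard error is then too large, its test rejects less often than 5% under the null, and a real difference is missed more often than it need be.

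The plan thus leaves out the clinician for two outcomes where it expects some between-clinician variation and doubts its power. What is at stake is the coverage of the promised intervals and the chance of seeing a real change in testing or return visits. The point does not concern the Cox model for time to diagnosis.

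**Working it through.** **Inputs**
- From Sample Size Justification: 33 clinicians, about 20 cases each, 10 per arm. 33 × 20 = 660, the plan's own total. Twenty cases make five blocks of four, so arms are balanced within clinician.
- The power behind the 660 concerns confidence and cannot be uniquely reproduced, because no baseline proportion is given. One assumption that fits is 55% vs 75%: 89 per arm × (1 + 9 × 0.3) = 89 × 3.7 = 329.3 per arm, about 660 in total. The plan gives no power figure for tests or visits.
- ICC (r) for tests and visits: not stated. The r = .3 in Sample Size Justification is for confidence ratings only. I take .05 to .3 as an assumed range.
- Two-sided 5% level, assumed from the 95% CIs.

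**Linear model (number of tests)**

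Let σ² be the total variance and N = 660.
- True variance of the arm difference: 4σ²(1 − r)/N.
- Variance that the plain model estimates: about 4σ²/N.
- Ratio of SEs: k = 1/sqrt(1 − r).
- Actual type I error: 2 × P(Z > 1.96k).
- Plain-model power where a clinician model has 80%: P(Z > 1.96k − 2.80).

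At r = .3: k = 1/sqrt(0.7) = 1.195 and 1.96 × 1.195 = 2.34. Type I error is 2 × P(Z > 2.34) = 0.019. Power is P(Z > 2.34 − 2.80) = P(Z > −0.46) = 0.677.

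| ICC (assumed) | CI too wide by | Actual type I error | Power, against 80% with clinician |
|---|---|---|---|
| .05 | 2.6% | 4.4% | 78.5% |
| .1 | 5.4% | 3.9% | 76.9% |
| .2 | 11.8% | 2.8% | 72.9% |
| .3 | 19.5% | 1.9% | 67.7% |

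A simulation of 33 × 20 cases with permuted blocks of four (4,000 runs per setting) agrees. At r = .3 the plain SE averaged 0.077 against a true SD of 0.065. Rejection under the null was 1.9% plain vs 4.8% with clinician, and power was 67.8% vs 79.6%. At r = .1 power was 76.8% vs 80.0%.

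These figures are for the bivariate model. If the multivariable model carries degree, specialty and years of experience, it recovers part of the between-clinician variance and the loss shrinks.

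**Logistic model (any unexpected visit by 30 days)**

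This was simulated on the same layout with 3,000 runs per setting. Risk is that of a control case with an average clinician, and the ICC is on the latent logistic scale. The comparator is a Mantel-Haenszel odds ratio stratified by clinician, standing in for a clinician model. The assumed log odds ratio is −0.75 at 10% risk and −0.5 at 30%.

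| Risk, ICC (both assumed) | Null rejection, plain vs stratified | Power, plain vs stratified |
|---|---|---|
| 10%, .05 | 4.1% vs 4.3% | 70.0% vs 70.2% |
| 10%, .1 | 3.8% vs 4.2% | 71.4% vs 72.0% |
| 10%, .3 | 2.9% vs 4.2% | 75.6% vs 79.7% |
| 30%, .1 | 3.8% vs 4.7% | 75.6% vs 77.6% |
| 30%, .3 | 2.5% vs 5.1% | 66.6% vs 73.9% |

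At 30% risk and ICC .3, under the null, the plain model's SE is 0.165 against a true SD of 0.147, so it is too large for its own marginal odds ratio. The stratified SE is 0.186, larger still, because the target has changed: with the effect present, the mean log odds ratio is −0.403 plain and −0.502 stratified. The gain shows as power and a correct error rate. The log-odds-ratio interval does not become narrower.

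**The case against.** The strongest objection is that this is brevity in a journal article. The abstract and the Primary Outcome section both state clustering by clinician, and the closing sentence of Exploratory Analyses does not even list the covariates of its multivariable model. If the clustering was meant to carry over, the problem disappears. But the section names two classes of model and attaches the clinician to only one, so an analyst who follows the text would fit plain regressions. The omission is an inference from that contrast, though a fair one.

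Several stronger readings are tempting and are not supported:
- A reader might infer that the plan expects clinicians to drive these outcomes. It says "we expect them to be highly variable both within and between clinicians". High variation within clinicians lowers the ICC, so this sentence does not imply a large one.
- A reader might take the 20% and 12-point figures as the expected loss. They use an ICC that the plan states only for self-rated confidence. At .05 to .1 the loss is 1 to 3 points.
- A reader might expect a narrower interval for the visit odds ratio. The simulation shows the opposite on the log scale.
- A reader used to cluster-randomised trials might fear false positives. Here treatment varies within clinician, and the error is on the conservative side.
- A reader might call these the trial's only between-arm measures of harm. The plan presents them as relevant to the diagnostic process, and it also compares time to diagnosis between arms.

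It also stands that the outcomes are exploratory. No confirmatory test or sample size depends on them, and the linear estimate itself is not biased.

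**Conclusion.** The point holds, with limited force. As written, the plan analyses test counts and unexpected visits without the factor within which cases were randomised. For test counts, the inflation of the interval follows directly from the balanced allocation. Its size depends entirely on an unstated ICC: negligible at .05 or below, and material from about .2 upward. For visits the plain test is conservative too. In the settings tried, the gain ran from 0.2 power points (10% risk, ICC .05) to 7.3 points (30% risk, ICC .3).

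The figures assume ordinary model-based standard errors, equal allocation within clinician, and 33 clinicians with 20 cases each. Severity is low: the change costs nothing and improves two exploratory analyses.

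**What to change.** Replace the closing sentence of Exploratory Analyses with wording such as: *The number of diagnostic tests will be analysed by linear mixed models and the occurrence of unexpected visits by 30 days by logistic mixed models, each with a random intercept for clinician, in both the bivariate and the multivariable versions. The odds ratio for visits is conditional on clinician.* This extends the clinician term that the section already uses for confidence and accuracy.

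The cost is this change of wording, with no new data, patients or staff. If visits are rare, the estimated clinician variance may fall to about zero, and the result then reverts to the plain logistic model.

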#### Multiple Hypothesis Testing

We will report the results of the hypothesis test for the primary outcome without adjustment for multiple hypothesis testing. No formal penalization for multiple hypothesis testing is planned for the secondary, subgroup, or exploratory outcome analyses, as we will treat them as exploratory and hypothesis generating. We will report 95% CIs for all point estimates.

#### Handling of Missing Data

Our general approach to missing data will be multiple imputation. It is possible that our primary outcome of diagnostic confidence will have a level of missing data, as it will depend on the response rate to survey questions. In addition to multiple imputation under the standard assumption that data are missing at random, given the covariates and outcomes that are observed, we will also implement sensitivity analyses using imputation under plausible missing-not-at-random scenarios. To maximize survey completion rates and thereby minimize the level of missing data, we will send 3 email reminders at 3 days, 7 days, and 14 days if the initial survey request was not completed. We will leave hard copies of the survey in clinicians’ mailboxes if the participants have not completed the online survey after the 3 email reminders.

#### Sample Size Justification

We planned our sample size using the primary outcome of clinician confidence in diagnosis, rated on a case-by-case basis. We anticipated an ability to detect (with 80% power) a 20% difference in clinicians rating their confidence in the case diagnosis as somewhat or very high, when comparing cases with versus without collective intelligence feedback. Assuming clustering of confidence ratings within clinicians at *r*=.3, we estimated that we need 33 clinicians with about 20 cases in total (10 with collective intelligence and 10 without collective intelligence; n=660 total cases).

#### Qualitative Analysis of Exit Interview

Qualitative analysis of interview transcripts will further examine barriers to usability and acceptance (ie, willingness to use) of the platform by clinicians in primary care clinical settings. Transcripts will be coded using an integrated inductive-deductive qualitative data analysis approach [21]. In particular, we will use the constant comparison method, an inductive qualitative data analysis approach in which data are broken down, compared for similarities and differences, and grouped together under similar conceptual themes [22] to uncover a wide variety of themes from the data, while also employing predetermined conceptual codes drawn from a modified TAM [23] to structure a deductive analysis of the data. A total of 2 study authors (KR and MH) will independently code the transcripts to identify preliminary themes through initial readings of the transcripts. Iterative discussions among all the study investigators will refine thematic categories and lead to a final set of salient themes identified across all the interviewees.

## Results

At the time of manuscript submission, the trial is actively enrolling participants, and the recruitment started on August 20, 2018. We have recruited 32 out of our recruitment goal of 33 participants at the San Francisco Health Network (SFHN) and UCSF Health primary care clinics. The majority of clinicians (25) work within the SFHN, and 7 are from UCSF Health primary care clinics. This study is funded until May 2020 and is approved by the UCSF Institutional Review Board (#17-23839) until January 2020. We have completed data collection as of June 2019 and will complete our proposed analysis by December 2019.

## Discussion

Diagnostic error is increasingly recognized as a significant public health concern. Extrapolations based on combining data from small studies suggest that approximately 12 million Americans experience a diagnostic error or delay every year in the ambulatory care setting [1]. However, to date, no prospective observational study of diagnosis in ambulatory care exists despite expert calls to address this important knowledge gap. Our study holds promise to close important gaps in the field of preventing diagnostic error in ambulatory care.

The study aims to improve diagnostic confidence in real-world ambulatory care settings using a collective intelligence technology platform that aims to assist primary care and urgent care clinicians in their diagnostic reasoning and decision making. Our robust mixed quantitative and qualitative analyses will help identify best use cases and clinical workflows for routine use of collective intelligence in ambulatory care. This work can then inform larger-scale work to estimate the impact of collective intelligence on diagnostic accuracy, and, ultimately, prevention of harm to patients. Findings will inform best practices to integrate digital health technology interventions for reducing diagnostic errors in primary care and urgent care clinics. This understanding can help with the adoption and tailoring of this and other collective intelligence platforms throughout safety-net health systems nationally.

## Appendix

Multimedia Appendix 1 Postvisit questionnaire.

Multimedia Appendix 2 Exit survey.

Multimedia Appendix 3 Interview guide for exit interview.

## Abbreviations

IT: information technology
MD: medical doctor
NP: nurse practitioner
NPS: Net Promoter Score
PEU: perceived ease-of-use
PU: perceived usefulness
SFDPH: San Francisco Department of Public Health
SFHN: San Francisco Health Network
T2Dx: time-to-diagnosis
TAM: Technology Acceptance Model
UCSF: University of California San Francisco
